## Study site

[figure not shown]

The study site is the Chiang Rai Health Center of the Thailand Ministry of Health and US CDC Collaboration (TUC)(described in more detail in section 2), located in Chiang Rai, Thailand. The TUC enjoys a strong working relationship with the Provincial Public Health Office and local public clinic sites including Chiang Rai Hospital.  TUC staff in Chiang Rai includes an international medical epidemiologist, a research coordinator, 5 research nurses, 4 research assistants, a laboratory scientist, and a data entry clerk, each of whom will spend half of their time working on this study while it is being conducted.  There is also strong administrative, laboratory, and data management support from the main office in Bangkok.  The group has extensive experience in performing cross-sectional and cohort studies including participant recruitment and follow-up, obtaining informed consent, interviewing, counseling, and referral, as well as performing pelvic examination, colposcopy, cervicography, and CVL. Clinic visits in this study will take place at the Chiang Rai Health Center (formerly the STD clinic) where the current phase I and II studies are being conducted and where the TUC has dedicated space for a research office, waiting room, laboratory, two pelvic exam rooms, and four counseling rooms.

## Study population

The study population will consist of 60 HIV-infected women, recruited from general medical and family planning clinics, persons living with AIDS groups, and if necessary, from public advertising. The study sample will not include minors, pregnant women, mentally retarded, or mentally disabled women.

## Eligibility criteria

Women will be eligible to participate in the study if they fulfill all of the following inclusion criteria:

- Age 18-50 years
- Plan to stay in the Chiang Rai area for at least four months
- HIV-infected, confirmed by Elisa and Western Blot tests
- Either has 1) no current sex partner and is planning to be abstinent for the study duration, *or* 2) has only one, HIV-infected sexual partner1 who is 18 years or older and is willing to give informed consent for confirmatory HIV testing and for the participant’s enrollment in the study. Women who have a steady partner/husband who she will not see during the study period or with whom she is not sexually active will not be required to bring their partner to the clinic for HIV testing and informed consent.
- Willing and able to give informed consent
- Willing and able to comply with the study protocol, including being tested for HIV and undergoing repeated pelvic and colposcopic examinations
- Willing to have male partner asked for informed consent because he will be exposed to study product
- Regular menstrual cycles (defined as occurring every 3-5 weeks, lasting 3-5 days) for the prior 3 months; if have amenorrhea or if using depo-provera, participant must have no reported history of vaginal bleeding for the previous 3 months
- CD4 count < 5002
- Not currently taking antiretroviral medications3
- Documented Class I or Class II (“atypical cells seen, usually caused by inflammation”) pap smear at screening for study participation
- In good health as determined by medical history, physical examination and results of any laboratory screening test, and the discretion of the clinical staff
- Able to achieve a score of 80% or better on true-false test of key study concepts. If women score less than 80% the first time they take the test, they may repeat the test at least one day later

1We are including this criterion to minimize any potential risk of HIV transmission from study participants to a sexual partner.

2We are including this criteria because women with CD4 counts greater than 500 are much less likely to have cervical-vaginal HIV shedding.

3We are including this criterion because women who are on antiretroviral therapy are much less likely to have cervical-vaginal HIV shedding. Women who begin antiretroviral therapy while enrolled in the trial will be allowed to continue to participate in the trial.

Women will be excluded from the study if any of the following **exclusion criteria** apply:

- CD4 count <50
- Pregnancy or desire to become pregnant in the next 3-4 months
- Delivery, miscarriage, or abortion within six weeks prior to study enrollment
- History of surgery on external genitalia, vagina or cervix in the month prior to study enrollment
- Existence of a clinically detectable genital abnormality, specifically warts or a congenital abnormality
- History of nonmenstrual vaginal bleeding with intercourse in past one month
- Current use of tampons, diaphragms, sponges, douching, or other intravaginal products. Women who are willing to abstain from using these products during the study will be included in the study.
- Concurrent participation in another trial of a vaginal product
- History of sensitivity or allergy to latex products (including gloves)
- Presence of epithelial disruption of the labia or genital mucosa visible to the naked eye at enrollment1
- Positive test for gonorrhea, chlamydial infection, trichomoniasis, or evidence of untreated syphilis (see section 5.19). Participants with positive tests must be treated and have a negative test of cure to be eligible for enrollment.1
- Positive tests for candidiasis or bacterial vaginosis (BV) *and* symptoms of vaginitis. Women may be enrolled after treatment if they are asymptomatic or have negative tests. Asymptomatic participants with positive tests for candidiasis or BV may be enrolled.

1If an RTI is diagnosed, treatment will be given, and the participant will be allowed to begin the study once she has completed treatment for the RTI and has had a test of cure. A clinically significant ulcer will be treated empirically for syphilis and chancroid (unless it is clearly herpetic), and she will be eligible for enrollment once the ulcer has resolved. Women with other persistent abnormal signs, such as vaginal or cervical discharge, despite treatment of the RTI will be eligible. Participants who test positive for an RTI must have a negative RTI test collected less than one month prior to her enrollment in the study. HPV detection will not be a criterion for exclusion if the women meet the Pap criteria for enrollment.

## Study recruitment

All HIV-infected women attending the recruiting clinics will be asked if they are interested in learning more about an opportunity to participate in a study of a vaginal product that may reduce HIV transmission. The following issues will then be reviewed:

- Study objectives
- Eligibility and exclusion criteria
- Study protocol requirements, including having a clinical evaluation three times per month for 3 months, inserting a vaginal product daily for 7 consecutive days each month, and having their partner tested for HIV and giving his informed consent (because of his exposure to the product).

If a woman is interested in participating, she will be given additional information regarding the study, and a screening appointment will be scheduled.

## Screening visit #1

The first screening visit at approximately day (–30) will include the following (see Tables 2 and 3):

- Interviewer-administered eligibility checklist
- Explanation of the study goals, methods, risks, and benefits
- Informed consent for screening
- Pre-test HIV counseling
- Blood draw for rapid plasma regain (RPR) test, HIV, and CD4 count
- HIV medical care referral (based on self-reported HIV status)
- Resources for additional information regarding the study

Information will be provided regarding study risks, benefits, and resources if participants have further questions regarding the study. At this time, women will also have an opportunity to discuss questions with a counselor in private. A screening interview will be conducted, and blood will be drawn for HIV, syphilis, and CD4 count. The woman will then be referred to Chiang Rai Hospital for an HIV medical care evaluation. Women will be taken to Chiang Rai Hospital by a study nurse with a referral letter and CRH Assessment form which will be carried in a sealed envelope.

If a woman is eligible and agrees to be screened for the study, a brief comprehension test will be administered after she has provided informed consent for screening and before she provides informed consent for enrollment to confirm that she understands the purpose of the study and the potential risks and benefits. If she scores over 80% on the comprehension test, written informed consent for the screening evaluation will be obtained. If she scores less than 80%, she will not be enrolled. She will be allowed to retake the comprehension test once, but it must be at least one day after the initial test.

## HIV evaluation

The HIV medical care evaluation will be conducted at The Department of Medicine at Chiang Rai Hospital and includes the following:

- HIV medical care review
- Assessment of eligibility for treatment with antiretroviral therapy
- Evaluation for tuberculosis preventive therapy

Participants will be referred to Chiang Rai Hospital for evaluation and treatment. Actual medicals costs incurred at Chiang Rai Hospital, including medical consultation, laboratory, radiology, and pharmacy fees, will be reimbursed by the study to the women for up to 1,000 Baht (approximately USD 22). In addition, the study will provide reimbursement for the nine-month tuberculosis prevention program for women who test positive for tuberculosis. Medicines for treating HIV infection will not be offered to participants as a part of this study.

Relatively few people with HIV/AIDS in Thailand have access to antiretroviral therapy (ART) through limited programs sponsored by the Ministry of Public Health. Currently the largest such program provides ART to approximately 2,500 people nationwide out of the estimated 600,000 people with HIV/AIDS in Thailand. Access to these programs is controlled by district-level committees. This situation is evolving with ART becoming more generally available. ART will not be offered to participants as a part of this study. Offering such therapy as a benefit of study participation could be an unduly coercive incentive to enrollment, forcing women who would not otherwise do so to use the study gel. In addition, provision of ART requires long-term commitment and rigorous attention to adherence, response to treatment, emergence of resistance, and monitoring for side effects, beyond the scope of this limited research protocol. During the study, staff will facilitate access to available ART programs for study participants in collaboration with the Chiang Rai Hospital Department of Medicine. If women are started on antiretroviral therapy during the initial HIV evaluation, they will not be eligible for the study. Participants will not be prevented or discouraged in any way from initiating antiretroviral therapy once they enroll, if it becomes available to them. If this occurs, participants will continue to follow the same procedures as those who are not on antiretroviral therapy; This procedure will be re-evaluated if the situation changes in Thailand, e.g., if access to antiretroviral therapy is expanded to make the medications available to most patients. Both the Community Advisory Group in Chiang Rai and the Thai Ethical Review Council support our plan.

The data collected from a woman who begins antiretroviral therapy will be analyzed and described separately from the other study participants because antiretroviral therapy will affect the amount of cervico-vaginal HIV shedding.

## Screening visit #2

The second screening visit, approximately day (–14) will include the following (see Tables 2 and 3):

- Review of study goals, methods, risks, and benefits
- Post-test HIV counseling
- Reproductive tract infection (RTI) symptoms, signs, and prevention counseling
- Family planning counseling
- Screening clinician form
- Urine pregnancy test
- Pelvic examination
- Pap smear
- Sample collection for RTIs
- Resources for additional information and/or complications and suspected side effects during the study

The study counselor will provide all women with intensive counseling regarding HIV and STI risk communication, partner HIV testing, condom use, and safer sex practices. Counseling will emphasize that abstinence or mutual monogamy is recommended. Male condom use for every sexual encounter will be strongly recommended to prevent transmission of different viral strains between partners, and proper condom use will be explained and demonstrated. Latex condoms, without N-9 lubrication, will be provided at no charge, and women will be asked to use only study condoms (to avoid possible confounding that might result from the use of N-9-lubricated condoms). STI signs, symptoms, and risk factors will be reviewed, and women will be counseled to continue their current method of family planning. Because the desire to become pregnant during the study period is an exclusion criterion for this trial, sexually active women not currently using a family planning method will be encouraged to adopt one, and will be referred to local family planning services if needed. If a woman does get pregnant during the study, she will be asked to immediately discontinue study product use. She will be referred for medical care and will be followed until the end of the study arm, then discontinued from the study, because pregnancy is an exclusion criterion for the study. If a woman meets study enrollment criteria, she will be asked to return to the clinic for enrollment 3-5 days after her next menstrual period has ended (or in 2 weeks [i.e., 4 weeks after her first screening visit] if she is using depo-provera). Sexually active women will be asked to abstain from unprotected vaginal intercourse for the 24 hours prior to each clinic visit. Women will also be asked not to douche or wash their genitals on study visit days.

For women for whom there is > 1 month between first and second screening visits, the eligibility checklist will be completed again at the second screening to confirm that her eligibility has not changed.

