Epithelial disruption is one of our primary endpoints, and a critical endpoint to assess in the evaluation of a new microbicidal agent (16). Studies of other vaginal microbicides (unrelated to Carraguard) have found increases in epithelial disruption with use in HIV negative women (e.g. Col-1492), potentially increasing their susceptibility to HIV.

There are no data indicating that patients enrolled in this or other microbicide studies are more susceptible to new strains of HIV. In addition, many of the participants in this study will not be sexually active, and those who are will be counseled regarding correct and regular condom use.

Reproductive toxicology tests in rats have been conducted using Carraguard™. Reproductive toxicology tests in rats consist of two segments: Segment I studies evaluate the effect of a product on fertility and early embryonic development up to implantation stage, and Segment II studies on implantation up to gestation. In Segment I studies, Carraguard™ had no adverse effect on fertility, implantation and behavior, even at high doses (final report pending).

In this study, there is an extremely small chance of gel use in very early pregnancy (women start using gel just after their period, and are using the gel for only one week in each cycle), and the segment I rat studies cover that period. The Population Council will seek an exemption for Segment II studies, based on Segment I results for Carraguard™, and existing reproductive toxicology results for carrageenan. The Population Council is asking for an exemption for segment II testing because Carraguard is not absorbed. However, if the US FDA does not grant an exemption, Segment II studies in rats will be conducted concurrently with the Phase III trial which will be conducted in Botswana and S. Africa, beginning late 2002- 2003. Notably, the FDA has asked the Population Council to allow HIV-negative pregnant women to continue to use gel during their pregnancy in the Phase III trial (indicating a low level of concern about teratogenicity of Carraguard).

There are no data indicating that patients enrolled in this or other microbicide studies are more susceptible to new strains of HIV.

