Follow-up visit #2 (day 14):

The second follow-up visit (day 14) (for those assigned to a product arm, this visit occurs7 days after the woman has stopped using the product), includes the following (See Tables 1-3):

- Pelvic examination
- Vaginal pool pH, and Gram stain specimen collection
- HPV testing
- Sample for cervico-vaginal HIV viral load
- Clinician study form

Women will then be asked to return to the clinic to begin the next study arm 3-5 days after the next menstrual period has ended.

Baseline visit:

The baseline visit will be the first visit of the new study arm. Women using depo provera will be placed on a regular 28 day schedule, so that day 0 will be approximately day 28 of the preceding cycle. In the event that a participant begins the study and she is unable to start her second or third study arms on time, we will allow the woman to start her next arm the following month. The Baseline visit, similar to the enrollment study visit, will include the following (See Tables 2 and 3):

- Interviewer-administered enrollment interview
- Collection of blood sample for plasma HIV viral load testing, HSV 1 and 2 antibody testing
- Baseline pelvic and colposcopic examinations
- Baseline sample collection for RTIs
- Baseline sample collection for cervico-vaginal HIV viral load
- Product administration (if a product arm)
- Second pelvic and colposcopic examinations (to assess acute effects of the product on the vaginal epithelium)
- Second sample collection for cervico-vaginal HIV viral load (to assess acute effects of the product on cervico-vaginal HIV viral load)
- Clinician study form

(The second examination and sample collection will not be conducted at the final study visit, day 28 of the third study arm).

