## Specimen collection and laboratory studies

The following samples will be collected for HIV and RTI testing when indicated in the protocol (see Table 2):

1. Blood (venipucture) for HIV and CD4 count will be conducted once at the beginning of the study.
2. HIV plasma viral load will be conducted at each baseline, a total of three times
3. Cervical/endocervical swab will be used to collect a pap smear specimen once at the second screening visit
4. Cervical swab for HPV testing at screening visit #2 and at each of the day 14 visits, a total of 4 swabs
5. Swabs (2) of the posterior fornix and endocervix for diagnosis of sexually transmitted infections will be collected at the second screening visit and day 28 of the 3rd arm, and repeated if signs or symptoms of STI develop during the study period (Total swabs’ 4).
6. Swabs (2) of the posterior fornix for Gram stain and pH, will be collected at each study visit in which an exam is conducted (Total swabs’22 )
7. Syphilis serologic testing will be conducted once at the beginning of the study unless a genital ulcer or other suggestive symptoms are identified
8. CVL specimens will be collected during each study visit in which a clinical exam is conducted, to measure cervico-vaginal HIV viral load by introducing 5 ml of PBS into the vagina and collecting the pooled fluid in the posterior vaginal fornix. A total of 16 CVLs will be obtained from each woman during the study.
9. Two vaginal swabs will be used during each pelvic exam during the study to collect cervico-vaginal HIV viral load samples (20 swabs). At the second exam (“acute effects” assessment) on day 0 of each arm, four swabs will be used to collect the cervico-vaginal HIV viral load samples (12 swabs)(Total swabs’ 32).

9) Urine pregnancy test at screening #2 and each baseline visit (4 urine samples)

10) Genital ulcer sample collection (if genital ulcer present clinically)

11) A swab will be collected at each study visit to test for semen contamination (11 swabs)

12) HSV-1 and HSV-2 serology on stored blood specimens from all baseline clinic visits (Total of 3 visits per woman - 180 stored specimens total).

13) Cytokine testing on stored CVL specimens from all baseline clinic visits and all day 7 visits (Total of 6 visits per woman - 360 stored specimens total).

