# Serious adverse events

A serious adverse event (SAE) or reaction which requires expedited reporting is defined by the U. S. Food and Drug Administration (FDA) as any untoward medical occurrence that:

- results in death or is life-threatening; (“Life-threatening” is defined as a SAE in which the patient was at risk of death at the time of the event. It does not refer to an event which hypothetically might have caused death if it were more severe);
- requires hospitalization or prolongs existing hospitalization;
- results in persistent or significant disability/incapacity;
- is a congenital abnormality/birth defect;
- jeopardizes participant health and required medical/surgical intervention to prevent serious outcome; or
- any other event that the investigator considered serious. (The Population Council also considers cancer and drug overdose as serious adverse events.)

Medical and scientific judgment should be exercised in deciding whether expedited reporting is appropriate in other situations, such as important medical events that may not be immediately life-threatening or result in death or hospitalization but may jeopardize the patient or may require intervention to prevent one of the other outcomes listed in the definition above. Generally, these should also be considered serious. Examples of such events are intensive treatment in an emergency room or at home for allergic bronchospasm; blood dyscrasias or convulsions that do not result in hospitalization; or development of drug dependency or drug use.

A probable relationship with the study product is *not* necessary to trigger reporting a SAE (i.e.car accidents still have to be reported if they reach the attention of the investigator).

All SAEs, whether or not related to study product use, must be reported by the investigator within 24 hours of his/her becoming aware of them to the Population Council SAE Desk [contact]), to the Population Council study coordinator, [name] [contact]), and to the CDC IRB. This reporting can be done by telephone, fax or email. The report of SAE by phone or fax must always be followed by a detailed written report, due within 7 days of the initial report. The Population Council study coordinator will inform the Population Council IRB. The local principal investigators will inform the U.S. CDC IRB and provide a Thai-language report to the Thai Ethical Review Committee.

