**Appendix 5: Table 2. Schedule of clinic visits and data collection**

| Study visit | Screen #1 | CRH referral visit | Screen #2 | Male  partner  visit | Enrollment | Follow-up #1 | Follow-up #2 | Baseline | Closing |
| --- | --- | --- | --- | --- | --- | --- | --- | --- | --- |
| Study day | ~ (-30) | ~ (-21) | ~ (-14) |  | Day 0 | Day 7 | Day 14 | Day 0/28 | Day 28,  3rd arm |
| Menstrual day (~28 day) |  |  | Mid-cycle |  | 3-5 days after menses | 10-12 | 17-19 | 3-5 days after menses |  |
| *Specimen collection* |  |  |  |  |  |  |  |  |  |
| HIV test | X |  |  | X |  |  |  |  |  |
| CD4 count | X |  |  |  |  |  |  |  |  |
| RPR | X |  |  |  |  |  |  |  |  |
| Urine preg test |  |  | X |  | X |  |  | X |  |
| HIV viral load |  |  |  |  | X |  |  |  |  |
|  |  |  |  |  |  |  |  |  |  |
| Pap smear |  |  | X |  |  |  |  |  |  |
| Gram stain, ph |  |  | X |  | X | X | X | X | X |
| Gonorrhea, chlamydia |  |  | X |  |  |  |  |  | X |
| Trich In-pouch test |  |  | X |  |  |  |  |  | X |
| Pelvic exam |  |  | X |  | X | X | X | X | X |
| HPV |  |  | X |  |  |  | X |  |  |
|  |  |  |  |  |  |  |  |  |  |
| Colpo |  |  |  |  | X (baseline)  X (15 min) | X |  | X (baseline)  X (15 min) | x |
| CV swab for HIV |  |  |  |  | X (baseline)  X (15 min.) | X | X | X (baseline)  X (15 min.) | X |
|  |  |  |  |  |  |  |  |  |  |
| CVL |  |  |  |  | X (baseline)  X (15 min.) | X | X | X (baseline)  X (15 min.) | X |
| Product application |  |  |  |  | X |  |  | X |  |

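### No pregnancy outcome is followed up although birth defect is an SAE criterion, and conceptions in the third arm have no scheduled pregnancy test

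*Protocol*

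**What the plan says.** Four parts of the protocol bear on this.

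- **Follow-up of a pregnancy** (Screening visit #2). A woman who becomes pregnant stops the product and gets a medical referral. The rule for her is then: "will be followed until the end of the study arm, then discontinued from the study, because pregnancy is an exclusion criterion for the study".
- **SAE definition** (Serious adverse events). One listed criterion is an occurrence that "is a congenital abnormality/birth defect". Every SAE, product-related or otherwise, goes to the sponsor within 24 hours once the investigator learns of it. No end date is given.
- **Testing** (Specimen collection and laboratory studies). "Urine pregnancy test at screening #2 and each baseline visit (4 urine samples". Table 2 in Appendix 5 agrees: the pregnancy row is marked at Screen #2, Enrollment and Baseline, and its Closing cell is empty.
- **Baseline visits of arms 2 and 3** (Follow-up visits). "The Baseline visit, similar to the enrollment study visit, will include the following", but the list that follows has no pregnancy test. The enrollment list does have one.

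On reproductive toxicology, the Background reports Segment I rat studies without adverse effect (final report pending). An exemption from Segment II is to be sought, and "if the US FDA does not grant an exemption, Segment II studies in rats will be conducted concurrently with the Phase III trial".

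**The concern.** An SAE criterion is useful only as far as the plan gives it a chance to be met and noticed. Here the criterion concerns a birth, and the follow-up rule stops months before any birth could occur. The list of study forms names no pregnancy or pregnancy-outcome form.

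Detection has a related gap. A conception in arm 1 or 2 meets a test at the next baseline. A conception in arm 3 meets none, although most women finish on a gel.

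What is at stake is safety information, which is the first objective. The animal studies of the period from implantation to gestation had not been done, so an exposed pregnancy would be scarce human data. As written, it would end in the record as a discontinuation with no outcome.

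**Working it through.** **1. Number of tests.** Screening #2 gives 1 and the three arm baselines (enrollment being the first) give 3: 1 + 3 = 4, the protocol's own figure. Counting closing as a baseline would give 5. The stated 4 and the empty cell in Table 2 therefore agree that no test is planned at closing.

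**2. Who finishes on a gel.** Four of the six sequences end in A or B: A-C-B, B-C-A, C-B-A and C-A-B. With 60 women spread equally, as the Sample size section intends, there are 60 / 6 = 10 per sequence.

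- Last arm is a gel: 4 × 10 = 40 women.
- Last arm is Carraguard (B-C-A, C-B-A): 2 × 10 = 20 women.

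**3. Planned follow-up against time to birth.** On the 28-day cycle of Table 1, closing falls on day 3 × 28 = 84. Follow-up after a pregnancy is recognised is at most about one arm, or 28 days. Time from conception to birth is not in the documents; I assume 252 to 280 days.

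| Conception on study day | Birth, days after closing |
|---|---|
| 0 | 252 − 84 = 168 to 280 − 84 = 196 |
| 70 | 70 + 252 − 84 = 238 to 70 + 280 − 84 = 266 |

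With the longest cycle that the eligibility criteria call regular (5 weeks), closing moves to 3 × 35 = 105 days, still well short of 252. No birth falls within planned follow-up.

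**4. Expected numbers.** The documents give no rates. I assume that 30% to 60% of women are sexually active, with 5% to 15% pregnancies per year among them, over about a quarter of a year.

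- All arms: 60 × 0.30 × 0.05 × 0.25 = 0.225, to 60 × 0.60 × 0.15 × 0.25 = 1.35.
- Third arm only (one third of the time): 0.225 / 3 = 0.075, to 1.35 / 3 = 0.45.
- Third arm, Carraguard only (20 of the 60 women): 0.075 / 3 = 0.025, to 0.45 / 3 = 0.15.

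Only the second and third lines bear on the missing closing test. The first bears on missing outcome follow-up, and it includes time on no product.

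**5. The baseline list.** The itemised list for the arm 2 and 3 baselines omits the test. The specimen section and Table 2 both require it there, and the list itself refers to Table 2.

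**The case against.** A reader might infer that a birth defect could never be recorded, so that the trial cannot satisfy its own SAE definition. The documents do not support that. The definition is a standard reporting trigger, not an endpoint to be ascertained. Reporting runs from the investigator's awareness with no cut-off, so a birth defect that comes to notice after discontinuation is still reportable. What is absent is any planned means of learning of it.

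A reader might also infer that third-arm pregnancies go undetected. That is too strong as well. A test is due at the third-arm baseline, before gel. The closing visit is timed to follow the next menstrual period, so a missed period would disturb the schedule, and closing includes a pelvic examination and an interview form. These routes are weakest for women with amenorrhoea or on depo-provera, whom the criteria admit, though the latter are using a contraceptive.

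Nor does the omission from the baseline list show that gel would start untested. Table 2 and the specimen section settle it, so it is a drafting slip to align.

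The sponsor also has a reasoned case that risk is low. Segment I covers early development, the Background says the product is not absorbed, and it reports that the FDA asked for pregnant women to be allowed to continue gel in Phase III. Wanting to become pregnant is an exclusion, condoms are free, and family planning referral is offered. All of this stands. It explains why few events are expected, but it does not supply an outcome for those that occur. The Background's reassurance about timing also assumes that gel starts just after a period, which does not describe women without periods. The contents of the study forms are not shown, so a form may ask more than its title suggests.

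**Conclusion.** The point holds as a gap in planned ascertainment. Birth defect is an SAE criterion, yet follow-up of a pregnant woman ends within about 4 weeks and no outcome is collected. No pregnancy test is scheduled after the third-arm baseline, when 40 of 60 women are assigned a gel course, 20 of them Carraguard.

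The size is small: about 0.2 to 1.4 pregnancies in the whole trial and 0.08 to 0.45 in the third arm. Both ranges rest on assumed activity and pregnancy rates. The conclusion that no birth falls within follow-up needs only that gestation is far longer than the study. No power, significance level or efficacy analysis is affected. This is a cheap improvement to safety ascertainment, not a defect that undermines the trial.

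**What to change.** Three edits:

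1. **Closing visit.** Add a urine pregnancy test to the Closing column of Table 2, and change the count in the specimen section from 4 to 5 samples.
2. **Screening visit #2.** Let study procedures end as planned, but state that the outcome of each pregnancy and the infant's status at birth will be collected by contact or from records, and reported under the SAE section where that criterion is met. Add a short outcome form.
3. **Baseline visit list.** Add the pregnancy test so that it agrees with the specimen section and Table 2.

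Cost: 60 more tests (300 instead of 240) at a visit already scheduled, one form, and a contact or record request for probably 0 to 2 women. The consent text may need a line to permit that contact. The drawback is that safety reporting for those women stays open after their last visit. Dose, product stopping and analysis are unchanged.
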